### Intervention—modifications

The intervention protocol is fixed and cannot be altered at the request of participants. No changes in intensity, session count, or scheduling will be allowed. Modifications are only permitted if visible motor twitches occur, in which case the stimulation intensity will be reduced, as described above.

### Intervention—concomitant care

No additional interventions or medications are restricted during the trial, except as defined in the eligibility criteria. Participants in both study arms may continue their standard care without modification.

### Criteria for discontinuation

Participants may be withdrawn from the study at the discretion of the investigators under the following circumstances: (i) Inability to complete the baseline MRI scan, (ii) occurrence of a clinical MS relapse, (iii) occurrence of a major adverse event or emergence of any new condition contraindicative to rTMS or MRI, and (iv) inability to comply with the intervention schedule or procedures.

All participants retain the right to withdraw from the study at any time, without providing a reason. Participants who have received at least one rTMS session will be included in the intention-to-treat analysis, provided data are available.

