### Strategies to improve adherence and participant retention

Participants, who have attended at least one rTMS intervention session, are encouraged to attend the follow-up visit regardless of the amount of intervention sessions completed. Participants who cancel with short notice will be contacted by phone and encouraged to adhere to the intervention. Should participants decide against participation in all intervention days, after initialising the intervention, they will be encouraged to attend as many sessions as they can. This is not considered as a modification of the protocol, but a reduced adherence to the full protocol.

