#### Statistical methods and analysis

All variables will be visually inspected for normal distribution through histograms and quantile-quantile plots prior to analysis and appropriately transformed if necessary. If data diverge from the normal distribution after transformation non-parametric testing will be performed. All tests will be 2-sided and statistical significance will be set at a *p*-value < 0.05. Data will be analyzed with R (116), Matlab (The MathWorks Inc., Natick, MA, United States) or similar software.

All data will be analyzed as a modified intention-to-treat, where all participants who have undergone at least one rTMS session (active or sham) and have follow-up data for outcomes will be analyzed according to the group they were randomized to. No per-protocol analyses are planned. The primary outcome will be analyzed as difference in change between baseline and clinical follow-up, between active and sham group. The statistical significance will be assessed with a mixed-effects linear model with the baseline as the reference. The primary analysis model will not adjust for depression, sleep, or physical activity measures, as the study is powered to detect overall treatment effects rather than covariate-adjusted effects. These variables will be examined in exploratory analyses as potential modifiers of treatment response, to assess whether treatment effects differ according to baseline levels or changes in these factors. Secondary outcomes with two timepoints (baseline and follow-up), will be compared as the difference in change between groups. Secondary outcomes with more timepoints will be analyzed with mixed-effects linear models with the baseline as reference. Neither the pre-registered primary or main secondary outcomes will be corrected for multiple comparisons, except where appropriate due to multiple measurements per participant. Exploratory analyses will be appropriately corrected for multiple comparisons prior to reporting.

There are no plans for predetermined subgroup analyses.

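### Investigator withdrawal is from the study, not only from stimulation or scanning; this conflicts with the retention rule on missed sessions and can cost the primary analysis randomised patients

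*Protocol article*

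**What the plan says.** Criteria for discontinuation opens with "Participants may be withdrawn from the study at the discretion of the investigators under the following circumstances" and lists four. The first is failure to complete the baseline MRI. Ground (ii) is a relapse of MS. Ground (iii) covers a serious harm, or a newly arisen condition that rules out stimulation or scanning. Ground (iv) is worded as "inability to comply with the intervention schedule or procedures". The same section later adds an inclusion rule: "Participants who have received at least one rTMS session will be included in the intention-to-treat analysis, provided data are available".

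The next section, Strategies to improve adherence and participant retention, says that participants with at least one session "are encouraged to attend the follow-up visit regardless of the amount of intervention sessions completed". Of those who do not attend every intervention day it says: "This is not considered as a modification of the protocol, but a reduced adherence to the full protocol".

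Statistical methods and analysis defines a modified intention-to-treat set: participants with at least one active or sham session who "have follow-up data for outcomes will be analyzed according to the group they were randomized to". It plans no per-protocol analysis. The primary outcome is the between-group difference in FSMC change from baseline to Day 11.

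**The concern.** An intention-to-treat comparison relies on outcomes being sought from everyone randomised, whatever happens to their treatment. Here the withdrawal rule is worded as leaving the study. It does not say that a patient who can no longer be stimulated or scanned may still complete a fatigue questionnaire. Even a new contraindication to MRI, which does not prevent anyone from filling in the FSMC, is a ground for leaving the study.

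Two things are at stake. First, investigators could treat the same patient differently and both follow the protocol: one withdraws a patient who cannot keep the schedule, the other records reduced adherence and books the Day 11 visit. Second, the listed reasons may be related to the outcome (a relapse could plausibly worsen fatigue) or to treatment (an adverse event could be caused by stimulation). Losing such patients can bias the comparison, and no later analysis can recover an FSMC that was never requested. There is also an effect on feasibility, which is assessed by drop-out rates between groups and by an interview with those who complete follow-up. Investigator withdrawals feed into the first and leave the second without the patients concerned.

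**Working it through.** **Which grounds matter after randomisation.** Allocation concealment and implementation places baseline MRI before group assignment, so ground (i) acts before randomisation. Grounds (ii) to (iv) can all arise between assignment on Day 1 and the primary follow-up on Day 11.

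**The sections side by side, for a patient who starts and then cannot attend all five days.**
- Intervention—modifications: session count and scheduling are fixed.
- Criteria for discontinuation, ground (iv): the patient may be withdrawn from the study.
- Retention section: the patient has reduced adherence and is encouraged to come to follow-up.
- Analysis section: the patient is analysed as randomised if follow-up data exist.

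The last two fit together. Ground (iv) does not fit with them, because using it normally ends the data collection on which inclusion depends. For grounds (ii) and (iii) there is no direct conflict with the retention section, which concerns the number of sessions. There the problem is only that withdrawal from the study is not separated from stopping a procedure.

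**The plan's own figures.** The inputs from Sample size calculation are a difference of 10 points, SD 12.5, 80% power and 15% drop-out; the 5% two-sided level is from the analysis section.
- Per arm: 2 × (12.5 × (1.960 + 0.842) / 10)² = 24.5, rounded up to 25, as stated.
- With drop-out: 25 × 1.15 = 28.75, rounded up to 29, as stated.

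The planned drop-out is 0.15 × 29 = 4.35, or about 4 patients per arm from all causes.

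**Illustration of the bias.** Assume that k of 29 patients in one arm are withdrawn without a Day 11 FSMC, that none are withdrawn in the other arm, and that the mean change of those withdrawn is D points worse than that of the rest of their arm. The analysed mean for that arm is then too favourable by (k/29) × D. Neither k nor D is given in the documents.

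| k | D = 10 | D = 20 |
|---|---|---|
| 1 | 0.34 | 0.69 |
| 2 | 0.69 | 1.38 |
| 4 | 1.38 | 2.76 |

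If there is no true effect, the standard error is 12.5 × √(1/(29 − k) + 1/29). For k = 4 this is 3.41, so a bias of 1.38 is 0.40 standard errors, and the two-sided type I error rises from 5% to about 6.9%. For k = 1 and D = 10 it is about 5.1%. The extreme corner, k = 4 and D = 20, gives about 12.8%.

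If withdrawals are equally frequent in both arms with similar outcomes, the two shifts cancel and the bias in the difference is about zero.

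**The case against.** The other side has several good points.

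- Both rules are permissive: one says that patients may be withdrawn, the other that they are encouraged to attend. A reader might infer an outright contradiction. The text supports a conflict to be reconciled, and only for ground (iv) once treatment has started.
- The discontinuation section itself keeps anyone with at least one session in the analysis when data exist. It nowhere says that a withdrawn patient gives no further FSMC. This stands as a matter of wording, but withdrawal from the study is the very event that would normally make the data unavailable.
- A reader might infer that the rule removes poor outcomes. The documents do not say how withdrawn patients fare. Relapse is the plausible case, the window to Day 11 is short, and recent relapse is an exclusion.
- A reader might also infer that the bias favours active stimulation. The documents do not support a direction. All personnel except the person who randomised are blinded, both arms receive the electrical scalp stimulation, and the sham side is built to match sound and feel. Mere discomfort is not a listed ground, and the background section calls serious events exceedingly rare. Relapses in the sham arm would act the other way. Blinding limits selective withdrawal, but it does not stop a treatment-related adverse event from triggering ground (iii).
- This is a condensed article, and the full protocol may describe data collection after withdrawal. The lack of that detail is therefore not the point. The point is a stated rule that sits badly with two other stated rules.

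**Conclusion.** The point holds in limited form. The withdrawal rule does not distinguish ending stimulation or MRI from ending follow-up. Ground (iv) conflicts with the retention section. Together with the requirement for follow-up data, the rule can take randomised patients out of the primary analysis for reasons that may be related to outcome or treatment.

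The size and direction of any bias are unknown. The range of about 0.3 to 1.4 FSMC points is an illustration that rests on three assumptions: losses in one arm only, 1 to 4 of them, and a change 10 points worse in those lost. It scales in proportion to that last figure and falls to about zero if losses are balanced and alike. It is not an estimate for this trial. Against a 10-point target the shift would be modest, but it is avoidable at little cost, so the text should be changed.

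**What to change.** Reconcile Criteria for discontinuation, the retention section and the analysis section. State that, for any participant who has received at least one session, stopping stimulation or MRI for whatever reason does not end outcome collection. FSMC is still requested at Days 6, 11 and 33 unless the participant withdraws consent, and it is analysed in the group assigned. When stimulation or scanning should stop is a matter for the sponsor and is not touched by this change.

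The cost is about one paragraph in an amendment. Days 6 and 33 are already completed electronically at home. Day 11 is a visit with tablet entry; where it cannot be attended, the existing e-mailed questionnaire link could be used. The small downside is a different collection mode for those few patients, which should be recorded and reported. The planned sample size does not change.

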### Strategies to improve adherence and participant retention

Participants, who have attended at least one rTMS intervention session, are encouraged to attend the follow-up visit regardless of the amount of intervention sessions completed. Participants who cancel with short notice will be contacted by phone and encouraged to adhere to the intervention. Should participants decide against participation in all intervention days, after initialising the intervention, they will be encouraged to attend as many sessions as they can. This is not considered as a modification of the protocol, but a reduced adherence to the full protocol.

### Primary outcome

The primary outcome of fatigue is measured as the difference in change in total FSMC (67, 68) score from baseline to follow-up at 6 days after the last rTMS intervention, between active and sham stimulation. Rating fatigue is largely subjective, and thus generally assessed as a patient-reported outcome (69, 70). However, the FSMC has the highest construct validity among often-used scales (69).

### Secondary outcome

#### 7 tesla proton magnetic resonance spectroscopy (^1^H-MRS)

The main secondary outcome is the between-group difference in changes in regional neurometabolite concentrations, specifically GABA and Glu, in the targeted left PMd, from baseline to the short-term follow-up on the final day of the intervention (Day 5). These concentrations will be assessed using ^1^H-MRS, acquired from a voxel positioned to cover the left PMd/M1 region. To assess neurometabolic network-level effects, an additional ^1^H-MRS voxel will be acquired in the contralateral (right) PMd/M1 region, to evaluate remote transhemispheric modulation. A voxel placed in the midline parietal region, will serve as a control site not expected to respond to the intervention. In addition to the short-term (Day 5) effects, longer-term effects will also be assessed at the primary follow-up 6 days post-intervention (Day 11), together with clinical outcome measures.

#### Fatigue and fatigability

Complementing the primary endpoint, between-group change in FSMC at 6 days post-intervention, we acquire additional secondary outcomes to assess both subjective fatigue and fatigability. Additional outcomes of subjective fatigue will be measured using the FSMC, at two additional follow-up timepoints: 1 day post-intervention (Day 6) and 4 weeks post-intervention (Day 33).

Objective fatigability will be assessed using the Fatigability Index (FI) (71–73), comparing the change from baseline (Day 0) to the primary follow-up (Day 11). Additionally, patient-reported fatigability will be evaluated using the Pittsburgh Fatigability Scale (PFS) (74, 75), with changes from baseline compared across three follow-up timepoints: Day 6, Day 11, and Day 33.

### Exploratory and other outcomes

#### Fatigue

Each subscale of the FSMC, cognitive and physical, will be analyzed separately as tertiary outcome measures testing for changes during the three follow-up timepoints relative to baseline. Acute fatigue will be quantified immediately before and after each rTMS session with a Visual-Analogue Fatigue Scale (76) assessing between-group differences in session-wise changes. Participants will also complete a fatigue diary during the intervals from baseline (D0) to the first intervention session (Day 1), and from the final session (Day 5) to the primary follow-up (Day 11). As no validated MS-specific fatigue diary currently exists, we will use a customized version adapted from a validated tool in oncology populations (77). Between-group differences in change in average daily fatigue scores will be assessed. To facilitate cross-study comparisons, participants will additionally complete the Fatigue Severity Scale (FSS) (78, 79) and the Modified Fatigue Impact Scale (MFIS) (80–82). These scales will be collected for reference purposes.

#### Depression, quality of life, and sleep

Depression will be assessed at baseline and the primary follow-up (Day 11) using the Major Depression Inventory (MDI) (53, 54), as depression is a key confounder due to its correlation with fatigue (83). Complementing the MDI, the Beck Depression Inventory-II (BDI-II) (84) will also be administered at both timepoints for cross-study comparability, and BDI-II data will only be reported descriptively.

The Multiple Sclerosis Impact Scale (MSIS-29) (85), and the Epworth Sleepiness Scale (ESS) (86) will be acquired at four timepoints [baseline; 1 day post-intervention (Day 6); primary follow-up (Day 11); and 4 weeks post-intervention (Day 33)], to assess the quality-of-life impact of MS (87), and undiagnosed sleep disorders (88), which might impact fatigue. Both scales will be analyzed as change-from baseline comparison between groups at the main clinical follow-up. Daily sleep quality ratings, integrated into the fatigue diary, will be analyzed analogously to diary-based fatigue scores.

#### Clinical tests and cognition

At baseline, participants will be assessed for their level of clinical disability, measured as the Extended Disability Status Scale (EDSS) (55) score. At baseline and follow-up, participants will complete the oral version of the Brief International Cognitive Assessment for Multiple Sclerosis (BICAMS) (89), comprising the California Verbal Learning Test (CVLT, recall 1-5) (90, 91), the revised version of the Brief Visuospatial Memory Test (BVMT-R) (92), and the Symbol Digit Modalities Test (SDMT) (93, 94). A modified Multiple Sclerosis Functional Composite (MSFC) (95), will also be administered, including the Timed 25-Foot Walk Test (T25FW) and 9-hole Peg Test (9HPT). The Paced Auditory Serial Addition Test (PASAT) will not be included due to overlap with SDMT, which demonstrates superior reliability (96, 97). All outcomes, SDMT, CVLT, BVMT-R, T25FW, and 9HPT, will be analyzed as between-group difference in change from baseline to main clinical follow-up.

#### Accelerometer-based outcomes

Participants will wear a wrist-mounted tri-axial accelerometer (wGT3X-BT, ActiGraph LLC, Pensacola, FL, United States) continuously from baseline until follow-up, including the intervention week. A meta-analysis of 21 studies with 1,098 subjects showed that people with MS are more sedentary and take fewer daily steps per day than healthy controls under free-living conditions (98). Higher daily physical activity in MS has been associated with lower fatigue levels (99, 100), independently of depressive symptoms (99). Given the sensitivity of wearable data to filtering and processing methods (101, 102), an exploratory analytic approach will be used to assess between-group differences.

#### Single-session outcomes of neurophysiology

All participants will undergo a neurophysiological assessment using TMS targeting left motor cortex immediately before and after the first intervention (D1). These measurements will evaluate cortical excitation-inhibition dynamics and serve both as exploratory biomarkers of fatigue mechanisms in people with MS and as indicators of functional target engagement induced by the paired-pulse low-frequency rTMS protocol. For acquisition specifics, we refer to the dedicated TMS-EMG section.

Single-pulse TMS will be used to measure the resting motor threshold (RMT), defined as the lowest stimulation intensity eliciting a motor evoked potential (MEP) of >50 μV in 5 out of 10 consecutive stimulations (103) and obtain input–output curves of mean MEP amplitudes at rest and during low-level muscle contraction (58). EMG recordings during contraction will used to derive the cortical silent period (CSP) in the contralateral and ipsilateral silent period in the ipsilateral hand (104). Paired-pulse TMS will evaluate short-interval intracortical inhibition (SICI) and intracortical facilitation (ICF) using established protocols, with 20 trials per condition to ensure reliability (58, 104).

#### Neuroimaging—structural and functional connectivity at ultra-high field (7 tesla)

Participants will undergo three MRI sessions using a 7T Philips Achieva scanner (Philips, Best, The Netherlands) at baseline, immediately after the final intervention (Day 5), and at primary follow-up (Day 11). For specific details on MR acquisitions, see later section.

At each timepoint, we will acquire ^1^H-MRS, for measures of GABA and Glu, diffusion-weighted imaging (DWI) for white matter microstructure and structural connectivity, and resting-state fMRI for functional connectivity analysis. Group comparisons will follow an exploratory longitudinal framework. In addition, structural whole-brain MRI images will be collected once across all the 3 scanning sessions for quantification of lesion load; tissue properties; and volumetric analyses. This includes MP2RAGE and 3D-T2 (on D0), 3D-FLAIR and multi-echo gradient echo scans (on Day 5), and double inversion recovery, magnetization transfer and multi-echo GraSE scans (on Day 11).

Missed sequences may be deferred to subsequent sessions or omitted entirely. Imaging data will contribute to exploratory analyses of fatigue-related neurobiology in MS.

#### Simulated E-fields

In addition to being an integral part of the intervention targeting algorithm, SimNIBS 4.5 allows for post-hoc simulation of the induced e-field for a given stimulation site. This allows important quality control for the *de facto* administered dose. The actual delivered electric field will be used in exploratory analyses of predictors of treatment effect.

#### Feasibility, side effects and adverse event monitoring

After every intervention session, participants will be asked to fill out the TMS Adverse Events and Associated Sensations Questionnaire (TMSENS_Q) (105), section 4 (and section 5 only in case of serious adverse events). This detailed questionnaire on adverse effects and sensations after TMS will provide detailed information on side effects to aid future decisionmakers. Feasibility will be assessed by drop-out rates between groups. Additionally, feasibility will be assessed by participants who complete follow-up through a semi-structured interview. This semi-structured interview is focused on the individual participant cost–benefit trade-off of effect against side effects of participation.

### Participant timeline

#### Trial overview

The trial consists of a baseline period; an intervention period; and a follow-up period. See Figure 1 for graphical synopsis of the study protocol, see Figure 2 for a flowchart for participants. See Supplementary Table S1 for an overview of when specific data are acquired and assessments are performed.

**Figure 1 fig1:**
[figure not shown]
Study overview, showing contents of each experimental day. TMS, transcranial magnetic stimulation; pp-rTMS, paired-pulse repetitive; MRI, magnetic resonance imaging; Q1, 1st at-home questionnaire; Q2, 2nd at-home questionnaire; DRCMR, Danish research center for magnetic resonance.

**Figure 2 fig2:**
[figure not shown]
Timeline for participants. rTMS, Repetitive transcranial magnetic stimulation; MRI, magnetic resonance imaging.

All participants will perform the baseline visit immediately after enrolment or at the latest within 1 month of inclusion. The baseline visit (D0) comprises clinical testing, multimodal 7T MR scanning to acquire baseline neuro-metabolite concentrations (MRS); functional connectivity (rs-fMRI) and structural connectivity (DWI). The baseline visit is performed in the week prior to the intervention week, at least 5 days before the first intervention day. Between D0 and the first intervention day, participants will wear a wrist-worn accelerometer and fill out a fatigue diary.

The intervention spans five consecutive weekdays. On the first intervention day (Day 1), additional TMS-based measures of cortical excitation-inhibition balance will be conducted before and immediately after the first rTMS intervention. On the last intervention day (Day 5), participants will immediately undergo post-intervention 7T MRI, including MRS, rs-fMRI and DWI The primary follow-up will be scheduled on Day 11, 6 days after the last rTMS session, and includes clinical assessments and the third 7T MRI scanning session with MRS, rs-fMRI and DWI. The timing of the follow-up visit, at 6 days post intervention, was decided for logistical reasons, and fall well within previously reported therapeutical after effects of neuromodulation in fatigue in MS (50, 106) and depression (107). Between Day 5 and Day 11, participants will continue wearing a wrist-worn accelerometer and complete a fatigue diary. Additionally, participants will be asked to complete electronic patient-reported outcome measures 1 day post-intervention (Day 6) and again 4 weeks after the final session (Day 33).

